## Method

### *Design*

This study will use primarily quantitative methodology with an experimental design. As a feasibility study for a RCT, we will use the CONSORT guidelines for randomised pilot and feasibility trials (Eldridge et al., 2016) to inform decisions around sample size, methodology and reporting.

Organisations called “sling libraries” loan out slings and carriers, offer advice and information on safe and functional sling use, and allow users to connect with, and support, one another. Sheffield Sling Surgery runs one of the largest sling libraries in the UK (<https://www.sheffieldslingsurgery.co.uk/>). They have agreed to provide hire slings, and sling training and support, for the duration of this study.

There are many different types of sling available (e.g. ring-sling, stretchy-wrap, structured carrier etc.) in order to suit different body shapes, postures, infant weights etc. “Sling” in this study refers to all sling types.

Participants will be randomised to either the intervention group, in which participants will be provided with a sling and training and support in how to use it safely and comfortably, or a wait list control (WLC) group, in which participants will receive the intervention following the final data collection time-point. Data will be collected online at three time points (pre-, mid- and post-intervention), using self-report measures. These data will be quantitative, however, we

will also include a number of brief, open-ended questions at the final data collection time-point, and the resultant data will be analysed qualitatively.

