One way in which a mother may increase close body contact with their infant, which may have similar benefits as skin-to-skin, is through the use of a "baby sling". This is a structured piece of fabric that allows the parent to carry their infant against their body (McGhee, n.d.).

Drawing from biopsychosocial models of depression, there are several mechanisms by which sling use might positively affect PND and maternal wellbeing.

*Biological: Hormonal Effects*

Close body contact between a mother and infant, such as that promoted by sling use, promotes the release of oxytocin in the mother (Uvnäs-Moberg & Prime, 2013). Oxytocin may reduce symptoms of those mental health difficulties which involve impaired social functioning, including depression (Cochran, Fallon, Hill, & Frazier, 2013; Domes, Normann, & Heinrichs, 2016).

*Social: Autonomy and Social Support Effects*

Self-determination theory notes that the absence of autonomy can lead to mental health difficulties (Deci & Ryan, 2008). Sling use allows the mother to have her hands free, and thus travel and carry out daily activities while holding her infant in close body contact (Blois, 2005). Sling use may therefore positively impact upon maternal wellbeing by providing this increased freedom and improving mothers' sense of autonomy, which in turn could reduce the risk of social isolation.

Additionally, sling use provides access to a range of social networks built around using slings (e.g. facebook groups and social meetings). Therefore sling use may also increase mothers' social opportunities and engagement.

*Psychological: Infant-parent Relationship and Interaction Effects*

An infant's attachment to the mother may contribute to the mother's experience of parenthood. For example, insecurely attached infants may cry more often than those who are securely attached to their parent (Belsky, Rovine, & Taylor, 1984).

Anisfeld et al., (1990) found that sling use may promote secure attachment in infants. Related to this, carrying has been found to reduce infant crying (Hunziker and Barr, 1986). Therefore, sling use may lead to a more positive parenting experience, building the number of positive interactions they experience, and consequently increasing feelings of parental self-efficacy (Jackson, 2000).

Altogether, by supporting each of these biopsychosocial factors, sling use may have a positive effect on symptoms of PND in mothers of young infants.

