### Inclusion Criteria

This study aims to recruit expectant mothers whose due dates fall within the expected baseline data collection period (late February 2019 to July 2019).

This study aims to recruit women who have not already been a regular sling user (e.g. with a previous infant).

Participants will need to be able to travel to Sheffield Sling Surgery (Sheffield city centre) where the intervention will take place. This includes all participants, as those randomised to the control group will receive the intervention following trial completion.

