### Exclusion Criteria

Participants will be excluded from this study if they have used a sling previously or attended an antenatal workshop at a sling library. They will also be excluded if their infant has a chronic or serious illness, or a disability. This is because the sling library have advised that that parent-infant dyads for whom this is the case often require a greater level of support and training when using a sling than this study would be able to provide (Knowles, 2016). Any participants who are interested in the study, but get excluded on this basis, by definition meet the inclusion criteria for the charitable “Building Bonds” scheme, currently running at the sling library, offering free sling hire, training and support specifically for families with chronic conditions and disabilities. These individuals would be referred to this scheme, and so will not be disadvantaged by the exclusion criteria.

As it is a feasibility study, this study has few inclusion and exclusion criteria. However data will be collected regarding any mental health diagnoses, number of children prior to their current infant, participant age, socioeconomic status, ethnicity, education level, postcode, and whether they are in a relationship or not. During data analysis, the impact of these factors upon the results of the study will be examined in order to potentially inform inclusion and exclusion criteria of future RCTs.

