Typically a parent or parents will sign-in, giving their name, email address, postcode, how they have travelled to the session, their child's name and age, and whether they require support that day). They will then be greeted by either a sling consultants or a voluntary peer supporter. On busy days there may be a short wait before someone is available to greet and work with the parent. At this point participants will state that they are a participant in this study. Following the session checklist, participants will be offered sling training and advice, and a sling use demonstration. Participants will learn how to safely use one of three different types of sling (either a stretchy, a close caboo, or one type of buckle carrier, dependent on the parent and infant's needs and preference) with a weighted demonstration doll before practicing with their own baby. Participants will be given this sling to hire for free for the duration of the study and a reminder leaflet containing sling safety information (Appendix U).

In these drop-in sessions, rather than being private 1:1 consultations, all contact between parents and Sling Surgery staff takes place within the same room. Thus while each parent, or set of parents, is met individually, if a number of parents have the same question, or a number are participants in this study, a Sling Surgery staff member may end up training, advising and demonstrating to a group of parents, rather than providing 1:1 support. Because everything takes place within the one room (aside from completion of the paperwork for hiring or buying a sling), this offers parents the opportunity to meet and support each other, and in particular discuss their experiences of sling use so far.

Following this session, participants will be sent an email which contains a link to a webpage with reminder information about their hire sling and how to use it, as well as an invitation to join the online sling community for further support, and information about the other support available through the sling surgery (Appendix U). Staff at the Sling Surgery will create a new “library” on their myTurn database in order to send these emails which are tailored to this study (e.g. which do not mention hire fees etc.).

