## Participants Needed - Free Sling Hire!

We are seeking  
volunteers for a  
maternal mental health  
and wellbeing  
research project.

[Images removed]

We are looking for women  
who are due to give birth  
between March 2019 and  
July 2019, and who have not  
used a baby sling before.

We want to see if using a sling might influence your mood, your  
general wellbeing, or your parenting experiences.

If you agree to participate:

- When your child is born, we would ask you to complete a set of online questionnaires 3 times over the course of 12 weeks.
- We would need you to travel to the Sheffield Sling Surgery for a one-off session where you will learn how to safely use a sling and be given a sling to hire for free for the duration of the study.
- You would be randomly assigned to one of two groups. For one group you will be asked to attend this session when your child is between 0 and 6 weeks old. If you are in the other group you will be asked to attend when your child is between 12 and 18 weeks old.

If you or anyone you know might be  
interested in participating, to learn more about it please email  
[name] (Trainee Clinical Psychologist and Principal  
Investigator) at:  
[[contact]](mailto:[contact])  
Contacting us in no way commits you to  
participate. And if you do agree to take part in this study, you can stop  
participating at any time.

This study has been approved by the University of Sheffield's Ethics Committee, reference 024147.

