## Appendix B Items for All Time Points

### Sling Use Measure

#### **Sling Use and Access to Sling Surgery Services**

Over the past 6 weeks, how often would you say that you have used your sling?

- ☐ Not at all
- ☐ Once or twice
- ☐ A few times
- ☐ About once a day
- ☐ About twice or three times a day
- ☐ More than three times a day

Over the past 6 weeks, how often would you say that you have used a pram or buggy (or similar)?

- ☐ Not at all
- ☐ Once or twice
- ☐ A few times
- ☐ About once a day
- ☐ About twice or three times a day
- ☐ More than three times a day

Over the past 6 weeks, how often would you say that you have accessed the sling surgery services (either online, in person, or other)?

- ☐ Not at all
- ☐ About once a week
- ☐ About twice a week
- ☐ Generally more than three times a week
- ☐ Daily

You will be now be asked the same questions again, but about your partner:

Over the past 6 weeks, how often would you say that your partner has used the sling?

- ☐ Not at all
- ☐ Once or twice
- ☐ A few times
- ☐ About once a day
- ☐ About twice or three times a day
- ☐ More than three times a day
- ☐ N/A

Over the past 6 weeks, how often would you say that your partner has used a pram or buggy (or similar)?

- ☐ Not at all

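### The protocol counts every carrier type as a sling, but the poster and use items as shown never tell women so; control-arm use may be undercounted

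*Protocol*

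**What the plan says.** The Design section gives examples of devices ("ring-sling, stretchy-wrap, structured carrier etc") and then states that the word sling "in this study refers to all sling types". Under Intervention, each woman learns to use one of three devices: "either a stretchy, a close caboo, or one type of buckle carrier". The session checklist in Appendix T offers the same three.

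The texts that women see are narrower:

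- The Appendix A poster seeks women who have not "used a baby sling before".
- Appendix B, whose items serve all time points, asks: "Over the past 6 weeks, how often would you say that you have used your sling". The partner item refers to the sling. Neither names carriers or gives examples.

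Prior use is an eligibility matter. The inclusion criteria seek women "who have not already been a regular sling user". The exclusion criteria state: "Participants will be excluded from this study if they have used a sling previously or attended an antenatal workshop at a sling library".

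Under Aims and Hypotheses, independent sling use by control participants is part of the feasibility focus. Under Proposed Analysis, the protocol says it may be helpful to repeat the analysis without control participants who used a sling.

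**The concern.** The exposure is defined broadly for the researchers but is asked about with a word that some women may read narrowly. Someone with a shop-bought buckle carrier may not think of it as a sling. She could then enter the study as a new user, or be recorded as a non-user while wearing the kind of device the other arm was given.

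Two quantities would be affected. The first is the reported rate of sling use among controls, which the study sets out to learn. The second is the re-analysis that removes control users: unrecognised carrier users would stay in the supposedly unexposed control group and dilute the contrast that this analysis is meant to isolate.

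**Working it through.** The protocol states no rate of carrier use or of misreporting, so there is no figure to reproduce. The check is mainly a comparison of texts.

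**1. Is the term ambiguous within the protocol?** The Design section says that sling libraries lend slings and carriers, naming two things, shortly before it puts structured carriers under the one word. The Abstract speaks of an infant carrier. The Introduction describes a baby sling thus: "This is a structured piece of fabric that allows the parent to carry their infant against their body". The receipt email in Appendix U calls the hired item a carrier. The authors and their delivery partner use the words interchangeably. Whether a new mother does so is not established.

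**2. Does the definition reach the woman in the text shown?** It is absent from the poster, the Appendix B items and the Appendix S templates. In the same Appendix B form, the pram item does add a catch-all for similar devices; the sling items do not.

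**3. Would anything else catch earlier carrier use?** The contact-details form in Appendix S does not ask about it. The Appendix O baseline questions ask about antenatal sling workshops only.

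**4. Does the risk differ by arm?** At T1 it should not, because intervention women complete baseline measures before their session. By T2 and T3, those who attended have been trained on the study devices, buckle carrier included. Controls are offered training only after T3. An error of this kind can only lower recorded use, so at T2 and T3 it would fall mainly on the control arm.

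**5. How large could it be?** This is an illustration only. Let *p* be true control use, *b* the share of those users whose only device is a structured or buckle carrier, and *m* the share of that group who would not call it a sling. All three are assumptions. The number of controls, *n* = 25-30, is from the Sample Size section.

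- Recorded use = *p*(1 − *bm*); users missed = *npbm*.
- Lowest case, *m* = 0: none missed, whatever *p* and *b* are.
- Middle case, *n* = 30, *p* = 0.40, *b* = 0.50, *m* = 0.50: recorded use = 0.40 × (1 − 0.25) = 0.30; missed = 30 × 0.40 × 0.25 = 3.
- Highest case tried, *n* = 30, *p* = 0.60, *b* = 0.50, *m* = 1: recorded use = 0.60 × 0.50 = 0.30; missed = 30 × 0.60 × 0.50 = 9.

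For comparison, the 95% half-width of a 40% rate is 1.96 × √(0.40 × 0.60 / *n*), which is 17.5 percentage points at *n* = 30 and 19.2 at *n* = 25. The middle case shifts the rate by 10 points.

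**The case against.** **No passage shows that women leave carriers out when asked about slings.** This stands. If all count them, nothing is missed. A reader might infer that control use *is* undercounted; the documents support only that it *may* be.

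**The definition may be given elsewhere.** The information sheet and consent form (Appendices Q and R) and the poster images are not in the text available for this review, and women receive study information before consenting. This also stands, so it cannot be said that the definition never reaches them. It does not settle the matter, because that information is given in pregnancy. The last use item is answered about 12 weeks after a baseline taken at 0-6 weeks, so up to about 18 weeks after birth, on a form that as shown carries no definition.

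**Unrecognised earlier users do not bias the comparison.** Correct: with 1:1 randomisation they fall into either arm by chance. They affect whether the sample matches the stated population, not the direction of the treatment contrast.

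**A reader might infer that a future trial would be planned too small.** The protocol does not support this. What it proposes to carry into later sample sizes are drop-out rates, standard deviations and preliminary between-group differences. An intention-to-treat difference already contains whatever dilution control carrier use causes, however that use is recorded. An understated requirement would arise only if a planner discounted an undiluted effect by recorded use, which the protocol nowhere proposes.

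**Sampling error is larger than the likely shift.** True in the middle case. But sampling error is shown by a confidence interval, whereas a one-directional recording error is not, and it can be reduced by wording alone.

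**Conclusion.** The point holds as a wording gap with a possible effect that differs by arm. The Design definition is not carried into the poster or the Appendix B use items as shown, so a woman who calls her device a carrier could pass the prior-use criterion or be recorded as a non-user. Recorded control use, and the re-analysis that depends on it, may be affected, with any error lowering control use more than intervention use at T2 and T3. The size cannot be determined from the documents; the 0 to 9 missed users above rest wholly on assumed values. The main intention-to-treat comparison is untouched by how use is recorded. This is a cheap improvement, not a flaw that undermines the study.

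**What to change.** State the Design definition, with its examples, in three places: on the poster, in the prior-use wording of the inclusion and exclusion criteria, and above the own-use and partner-use items at T1, T2 and T3. For example: *By sling we mean any type of sling or baby carrier worn to hold your baby, including ring slings, stretchy wraps and structured or buckle carriers.* Word the use items as *a sling or carrier*. Keep to the protocol's own scope: a qualifier such as *soft* would set a boundary that the Design section does not contain.

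The cost is a sentence or two on the poster and in the Qualtrics forms. A few women with earlier carrier use may be screened out, which could slow recruitment slightly.

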### *Sample Size*

With regards to sample size, as this is a feasibility study and hypothesis testing is not the primary aim, a normal power calculation need not be undertaken (Eldridge et al., 2016; Williams, 2016). Instead the sample size should be selected based on whether it can adequately estimate parameters that will support the design of future RCTs, e.g. recruitment rates, treatment adherence, completion rates of outcome measures etc. Furthermore it is common for the sample size of a feasibility study to be influenced by practical considerations, such as demands on time and resources (Eldridge et al., 2016).

With these considerations in mind, and following the recommendations of the National Institute of Health Research (NIHR: Research Designs Service; Hooper, 2014), it was estimated that a sample size of 50-60 participants (25-30 per condition) is likely to be both feasible and able to accurately estimate parameters for future RCTs, such as drop-out rates and standard deviations which could be used to determine future sample sizes.

### *Participants*

Participants will be pregnant women with a due date that falls in the T1 data collection window (see below). Participants will be recruited via the following methods:

- 1) The national charity, The National Childbirth Trust will ask their Sheffield teachers to hand out our flyers at their group classes.
- 2) Flyers will also be distributed in locations likely to be frequented by expectant mothers. For example, shops selling baby-care products, community centres, libraries, hypnobirthing classes

etc.

Representatives from NCT have already agreed to assist with recruitment. Recruitment materials may be found in Appendix A.

### Inclusion Criteria

This study aims to recruit expectant mothers whose due dates fall within the expected baseline data collection period (late February 2019 to July 2019).

This study aims to recruit women who have not already been a regular sling user (e.g. with a previous infant).

Participants will need to be able to travel to Sheffield Sling Surgery (Sheffield city centre) where the intervention will take place. This includes all participants, as those randomised to the control group will receive the intervention following trial completion.

### Exclusion Criteria

Participants will be excluded from this study if they have used a sling previously or attended an antenatal workshop at a sling library. They will also be excluded if their infant has a chronic or serious illness, or a disability. This is because the sling library have advised that that parent-infant dyads for whom this is the case often require a greater level of support and training when using a sling than this study would be able to provide (Knowles, 2016). Any participants who are interested in the study, but get excluded on this basis, by definition meet the inclusion criteria for the charitable “Building Bonds” scheme, currently running at the sling library, offering free sling hire, training and support specifically for families with chronic conditions and disabilities. These individuals would be referred to this scheme, and so will not be disadvantaged by the exclusion criteria.

As it is a feasibility study, this study has few inclusion and exclusion criteria. However data will be collected regarding any mental health diagnoses, number of children prior to their current infant, participant age, socioeconomic status, ethnicity, education level, postcode, and whether they are in a relationship or not. During data analysis, the impact of these factors upon the results of the study will be examined in order to potentially inform inclusion and exclusion criteria of future RCTs.

### *Service User Involvement*

Collaborators for this study include the National Childbirth Trust (NCT), as well as the local sling library.

The NCT provides independent information to parents, and also helps parents to connect with local parent support groups in order to gain both practical and emotional support (NCT, n.d.). The NCT have agreed to assist in the recruitment of participants for this study who are not already sling users.

This project has developed, in part, through pre-existing collaboration between the project supervisor and the local sling surgery and library. The sling surgery has helped to develop the design of this project from its earliest stages.

Furthermore, it is hoped that, through these organisations, it will be possible to send an example battery of measures to both sling users and non-sling users in order to receive feedback around whether the battery as it stands looks too onerous, or time consuming, for mothers who have recently given birth, to complete.

## Measures

All measures are self-report and will be completed online using the programme

Qualtrics.

At this stage in the research process a number of measures have been selected to be administered to participants. As mentioned in the “Service User Involvement” section above, it is hoped that service users might feedback on whether, as it stands, this battery of measures is currently too onerous for participants to complete, particularly as baseline measures are due to be completed soon after childbirth. Thus while the full battery of possible measures is presented here, some of these measures may be omitted from the final battery administered to participants, based on service user feedback as well as the judgement of the researchers and staff at the sling surgery.

Primary Measures

*Sling Use and Support*

With the support of the sling surgery, as in previous studies (Anisfeld et al., 1990), an idiographic measure has been designed, asking participants how often they have used their sling over the past 6 weeks (please see Appendix B).

For comparison, participants will also be asked how often they have used a pram or stroller over the same time period.

This measure also asks participants how often they have accessed the services of the Sling Surgery over the past 6 weeks, or any other sling-related support.

Participants will be asked how often their partner has used a sling, pram, or accessed the Sling Surgery Services over the past 6 weeks, so that this information may be taken into account. This is partly in order to account for partner sling use as a possible confounding variable when analysing the results of the study, but it also acts as a way of capturing paternal involvement and use of slings, which may be of interest in future research.

At T2 and T3, participants will be asked whether they have swapped their sling over the past 6 weeks (the course of the study since the previous data collection time-point), and if so, how often they have done so.

The time period which all of the above questions refer to (6 weeks) may be altered according to feedback from the Sling Surgery and service users.

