## Aims and Hypotheses

A feasibility study is underpowered to reliably assess treatment effectiveness (Williams, 2016). Therefore the primary focus of a feasibility study is not hypothesis testing, though statistical analysis of between-group outcome differences may be conducted in a preliminary way in order to inform the sample size calculations of future RCTs (Williams, 2016). Instead, as a feasibility study, the focus of this study is on collecting information that will support the design of future studies, e.g. recruitment rates, treatment adherence etc.

The primary aim of this study is therefore to examine whether it is possible to conduct an RCT with this population (mothers of new-born infants) and intervention (sling use, training and support). This study has a particular focus around the feasibility of recruitment of this population and also around treatment fidelity, including whether control group participants independently engage in sling use during the trial.

While this study is underpowered to draw definitive conclusions around treatment effectiveness, it is predicted that sling use will lead to lower Postnatal Depression scores (as measured by the Edinburgh Postnatal Depression Scale (Cox, Holden, & Sagovsky, 1987), and higher wellbeing scores (as measured by the Warwick Edinburgh Mental Wellbeing Scale (WEMWBS); Tennant et al., 2007), parenting self-efficacy and responsiveness (as measured by the Parenting Sense of Competency Scale (PSCS); Gibaud-Wallston & Wandersman, 1978; and Caregiving Experiences Questionnaire (CEQ); Brennan, George & Solomon, 2013), and breastfeeding frequency and duration, in the intervention group, compared to the control group. It is predicted that any improvement seen in the scores on these measures post-intervention, in comparison to pre-intervention scores, will be significantly greater for intervention group participants, than any improvement seen for control group participants.

A secondary hypothesis is that maternal attachment style (as measured by the Experiences in Close Relationships Scale-Short (ECR-S; Wei, Russell, Mallinckrodt & Vogel, 2007) might act as a moderator of the relationship between sling use and the scores on these various measures.

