## Research Protocol

- ☐ Once or twice
- ☐ A few times
- ☐ About once a day
- ☐ About twice or three times a day
- ☐ More than three times a day
- ☐ N/A

Over the past 6 weeks, how often would you say that your partner has accessed the sling surgery services (either online, in person, or other)?

- ☐ Not at all
- ☐ About once a week
- ☐ About twice a week
- ☐ Generally more than three times a week
- ☐ Daily
- ☐ N/A

Over the past six weeks, have you needed to swap your sling for a different one, and if so, how many times have you swapped slings?

- ☐ I have not swapped slings.
- ☐ Yes, I have swapped slings once.
- ☐ Yes, I have swapped slings twice.
- ☐ Yes, I have swapped slings three times.
- ☐ Yes, I have swapped slings more than three times.

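### The sling-use form omits the outside-support question that the Measures section describes, and its sling wording may lead some controls to under-report independent sling use

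*Protocol*

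**What the plan says.** In the Protocol, Measures (Sling Use and Support), the use measure is described as "asking participants how often they have used their sling over the past 6 weeks (please see Appendix B". On support, the same section says participants are asked "how often they have accessed the services of the Sling Surgery over the past 6 weeks, or any other sling-related support". For the partner, it refers to use of *a sling*, use of a pram, and access to the Sling Surgery.

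Appendix B is the form itself. Its own-use item reads "Over the past 6 weeks, how often would you say that you have used your sling". Its own-support item reads "how often would you say that you have accessed the sling surgery services (either online, in person, or other". Its partner-support item reads "how often would you say that your partner has accessed the sling surgery services (either online, in person, or other". The partner-use item asks about *the sling*.

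Aims and Hypotheses gives treatment fidelity as a particular focus, "including whether control group participants independently engage in sling use during the trial". Control Participants gives both arms the same measures at the same time points. Proposed Analysis suggests a re-analysis without controls who used a sling or had contact with the Sling Surgery.

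**The concern.** The text and the form do not match. The text describes a question about support from any source, and the form has none. Support matters here because the Aims define the intervention as sling use, training and support together, and the Introduction offers sling-based social networks as one route by which slings might help mothers. The Design section describes sling libraries as a class of organisation, of which the Sheffield one is an example, so other sources plainly exist. The intervention arm is directed to the Sling Surgery, while controls are not offered it until after the last assessment. The unrecorded sources are therefore mainly those a control would turn to.

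The sling wording adds a second difficulty. The form asks about *your sling*, and a control has been given none. If some controls read the item as not applying to them, the answer to a stated feasibility question would err on the low side. Neither gap can be closed by analysis, since a question that was not asked leaves nothing to analyse.

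**Working it through.** No figure in the plan bears on this, so the check compares the passages.

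**Support.**

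1. Appendix B has seven items: the mother's sling use, pram use and Sling Surgery access; the same three for the partner; and sling swaps.
2. In both access items, the words in brackets list ways of contacting the Sling Surgery. They do not name another provider.
3. Other instruments do not fill the gap. The antenatal sling workshop question in Appendix O is asked at baseline only and concerns the time before birth. The open questions at T3 in Appendix P concern the Sling Library and Sling Surgery. Data Collection, listing the T1 and T2 content, also mentions only Sling Surgery services.
4. Outside support is therefore not recorded at any time point, although the Measures section says it is.

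**Sling use.**

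| Source | Mother | Partner |
|---|---|---|
| Measures | *their sling* | *a sling* |
| Appendix B | *your sling* | *the sling* |
| Proposed Analysis, exclusion of controls | *a sling* | separate re-analysis |

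5. For the mother, the text and the form agree with each other, but both are narrower than the rule that uses the answer. For the partner, the text and the form differ.
6. The pram item on the same form is open to any pram, buggy or similar. The sling item is not worded in that way.
7. Study messages use *your sling* for the hired one: the T2 closing page for the intervention group (S.10), and the control group's messages after T3 about returning the sling (S.13 and S.14). The swap item fits the same reading.
8. The own-use item has no not-applicable option, so a control with no issued sling who finds the item irrelevant would most naturally tick the lowest category. A control who borrowed a carrier could do the same.

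**Sensitivity of the rate.** Sample Size plans 25 to 30 women per condition. If all controls answer, one misclassified woman changes the observed proportion by 1/30 = 3.3 to 1/25 = 4.0 percentage points. This shows how sensitive the rate is; it does not estimate how many would be misclassified.

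**The case against.** The strongest reply is that the planned contamination measure survives. The Aims ask about controls' sling use, and the Proposed Analysis excludes controls on sling use or Sling Surgery contact. Both have items. A control who gets help elsewhere and then uses a sling should be picked up by the use item. This stands: the missing support item does not by itself lower the contamination rate.

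The second reply concerns *your sling*. A carrier that a control has bought is literally hers. The form is headed for all time points and a sling-use measure is planned at baseline, when nobody yet holds a study sling, so the words cannot mean only the study's. The Design statement that the term "in this study refers to all sling types" concerns types, not ownership, so its absence from the form proves nothing about source. All of this stands. What is left is ambiguity, chiefly for a borrowed sling. Under-reporting is a risk and has not been shown.

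The Measures section also allows measures to be dropped after service user feedback. That does not explain the mismatch, because the text describes the designed measure as already asking about other support.

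A reader might go further and infer that contamination will be understated by a material amount, and that a later trial planned on it would be too small. The documents do not support this. They give no contamination rate and no rate of non-capture. The Aims let preliminary between-group differences inform later sample sizes, and the Proposed Analysis is by intention to treat. Such a difference already contains any dilution from controls who used slings, recorded or not, and inflating it again for contamination would count the dilution twice.

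**Conclusion.** Two points hold. First, Measures and Appendix B contradict each other on outside support and must be reconciled; as the form stands, that support is not recorded. Second, the wording of the two use items is narrower than the rule they serve, so independent sling use by controls may be under-reported. The direction rests on the assumption that some controls read *your sling* as a sling issued or owned; the size cannot be derived from the documents.

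A reader might also conclude that contamination should be redefined to include outside support or partner use. That does not follow. The Aims concern the control's own sling use, the Proposed Analysis adds only Sling Surgery contact, and partner use has its own re-analysis there. The correction is worth making because it costs little, concerns a stated feasibility question, and cannot be made once the data are collected.

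**What to change.** In Appendix B, for both arms:

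- Reword the own-use item to ask about *any sling or baby carrier, whether your own, borrowed or hired*, and reword the partner-use item in the same way. Bring the matching sentences in Measures into line.
- Add one closed item on sling-related support from anyone other than the Sling Surgery, as Measures already describes.

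Keep the contamination rule as it stands in the Aims and Proposed Analysis: the control's own sling use, or her contact with the Sling Surgery. Report outside support and partner use separately, as descriptive results.

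The cost is two reworded Qualtrics items and one further closed question, a small burden. The reported contamination rate may come out higher than it would under the present wording.
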